**Fig. 1 Fig1:**
[figure not shown]
The flow chart of the current trial

### Patient selection

#### Inclusion criteria

Histopathologically confirmed primary prostate cancerStage cT1-3N0M0 at the time of initial diagnosis, with solid prostate tumor visible on both multiparametric magnetic resonance imaging (mpMRI) and 68GA-PSMA PET/CT imagingAge between 45 and 85 yearsNo regional lymph node metastasis and distant metastasis confirmed by CT, MRI, bone scan, and PET/CT (PSMA)No metal implants such as artificial hip joint in the irradiation field or in the irradiation pathway that can significantly affect the dose distributionECOG 0 ~ 2; No complications that might affect radiotherapy such as severe pulmonary hypertension, cardiovascular disease, peripheral vascular disease, or serious chronic heart disease; heart function grade 1 (according to the NYHA classification grading of cardiac function)Acceptable hematopoietic function and liver/kidney function:Hematopoietic function: hemoglobin ≥ 90g/L, platelet ≥ 70 × 10^9^/L, white blood cell ≥ 3 × 10^9^/LLiver function: ALT and AST<1.5 times of upper limits of normal (ULN), bilirubin < 1.5 × ULNRenal function: serum creatinine ≤ 140 μmol /LSigned written informed consent

#### Exclusion criteria

With other uncontrolled primary malignanciesWithout pathology diagnosisPathological types of non-adenocarcinoma of prostate (such as small cell carcinoma, sarcoma, etc.)Lymph nodes or distant metastasisPrevious prostatectomy or pelvic radiotherapyObvious adverse effects related to previous treatment, such as urinary incontinence, hematuria, and bloody stools, which may be aggravated or induced by radiation therapyActive medical implants, e.g., pacemaker and defibrillator, which may be interfered with the normal function by high-energy radiation or may affect the dose in the target areaDrug abuse or alcohol dependenceHIV positive, including previous antiretroviral treatment; syphilis active stage; chronic hepatitis B, virus replication period; active stage of hepatitis CA history of mental illness, which may hinder the completion of treatmentPoor general health, i.e., KPS<70 or ECOG>2With serious complications that may interfere with radiotherapy, including:Unstable angina pectoris, congestive heart failure, or myocardial infarction requiring hospitalization in the past 6 monthsAcute bacterial or fungal infectionExacerbation of chronic obstructive pulmonary disease or other respiratory diseases requiring hospitalizationInflammatory bowel disease or connective tissue disease, such as active scleroderma and lupus (contraindicated by radiotherapy)Liver dysfunction (ALT and AST≥ 1.5 × ULN, bilirubin ≥ 1.5 × ULN)Immunosuppressed patientThe presence of other disorders or other factors that may affect proton or carbon ion therapyWithout civil capacity or with limited civil capacity

### Patient assessments

When patients meet the trial conditions, they are provided with relevant information including potential risks and benefits of participating in the trial. Patients may be enrolled and randomized by the principal investigator in this trial once written consent has been obtained and all required documentation will be provided by SPHIC. Patients will be randomly assigned to either arm A or arm B in a 1:1 ratio using computer-generated random numbers by the principal investigator, and sequentially numbered after being randomly assigned. Before radiation, a detailed medical history inquiry and physical examination are required. Pathological diagnosis of the primary disease, including pathological classification, Gleason score, and positive puncture rate, is necessary before treatment. Also, patients need laboratory tests, such as peripheral blood routine, serum chemistry, urine and stool routine examination, the levels of prostate-specific antigen (PSA), fPSA, testosterone, neuron-specific enolase (NSE), and tests for HIV, syphilis, hepatitis. In addition, CT of the chest, mpMRI of the prostate, and B-scan ultrasonography of upper abdomen and inguinal and supraclavicular lymph nodes are conducted before irradiation. Bone scan and 68Ga-PSMA PET/CT are performed to comprehensively evaluate the lesion range and staging. Cardiac function examinations including electrocardiogram are taken and cardiac ultrasound, 24-h Holter examination, and coronary angiography are conducted if necessary. Moreover, the effects of carbon ion therapy on quality of life are evaluated by the five-dimensional European quality of health scale (EQ-5D), International Prostate Symptom Score (IPSS), and Expanded Prostate Cancer Index Composite (EPIC) questionnaires.

During irradiation, all patients are regularly assessed for acute toxicities of normal tissues at least once a week until they have subsided. The adverse events, grading, and correlation with radiotherapy are documented at each evaluation. Specific evaluation contents include weekly routine blood tests to observe the hematological toxicity, monthly liver function tests to observe the liver toxicity, weekly routine urine examination to observe the occurrence of hematuria and urinary tract infection, IPSS questionnaire to evaluate urinary system toxicity, and weekly routine stool examinations and occult blood examinations combined with the symptoms of intestinal toxicity to exclude radioactive enteritis. Patients are treated with combined endocrine therapy, either neoadjuvant endocrine therapy or concurrent endocrine therapy, depending on their grading. When necessary, a supportive medication is initiated or adapted. When patients experience treatment-related adverse events, appropriate medications will be given according to the severity of the disease. If patients have an unexpected injury during the clinical study, financial compensation will be made in accordance with Chinese laws and regulations. Additionally, quality of life is collected during and at the end of radiotherapy. Table 1 summarizes the schedule.

**Table 1 Tab1:** Schedule of the trial

	Before radiation	During radiation	At the end of radiation (the final day of radiation)	Follow-up after treatment						
		Every week		The first year				The second and third years	The fourth year	From the fifth year
				Weeks 4–6 (first time)	The 3rd month	The 6th month	The 12th month	Every 3 months	Every 6 months	Every year
**Written informed consent**	**√**									
**Medical history/physical examination**	**√**	**√**	**√**	**√**	**√**	**√**	**√**	**√**	**√**	**√**
**KPS, ECOG**	**√**	**√**	**√**	**√**	**√**	**√**	**√**	**√**	**√**	**√**
**Pathological diagnosis**	**√**									
**Inclusion and exclusion criteria**	**√**									
**Peripheral blood routine examination**	**√**	**√**^**a**^	**√**	**√**	**√**	**√**	**√**	**√**	**√**	**√**
**Serum chemistry**	**√**	**√**^**a**^	**√**	**√**	**√**	**√**	**√**	**√**	**√**	**√**
**Urine and stool routine examination**	**√**	**√**^**a**^	**√**	**√**^**a**^	**√**^**a**^	**√**^**a**^	**√**^**a**^	**√**^**a**^	**√**^**a**^	**√**^**a**^
**Levels of PSA, fPSA, testosterone, and NSE**	**√**		**√**	**√**	**√**	**√**	**√**	**√**	**√**	**√**
**Tests for HIV, syphilis**	**√**									
**Tests for HBV, HCV**	**√**									
**Cardiac function examination**	**√**									
**CT of the chest**	**√**						**√**	**Annually**	**Annually**	**Annually**
**CT scan or ultrasound of the abdomen**	**√**		**√**	**√**	**√**	**√**	**√**	**√**	**√**	**√**
**mpMRI of prostate**	**√**		**√**	**√**	**√**	**√**	**√**	**Annually**	**Annually**	**Annually**
**Bone scan examination**	**√**^**a**^						**√**	**Annually**	**Annually**	**Annually**
**68Ga-PSMA PET/CT**	**√**^**b**^		**√**^**b**^				**√**	**Annually**	**Annually**	**Annually**
**Evaluation of acute toxicities (NCI-CTACE)**	**√**	**√**	**√**	**√**	**√**			**√**		
**Evaluation of late toxicities (RTOG/ EORTC)**					**√**	**√**	**√**	**√**	**√**	**√**
**EPIC**	**√**	**√**	**√**		**√**	**√**	**√**	**Annually**	**Annually**	**Annually**
**EQ-5D**	**√**	**√**	**√**		**√**	**√**	**√**	**Annually**	**Annually**	**Annually**
**IPSS**	**√**	**√**	**√**		**√**	**√**	**√**	**Annually**	**Annually**	**Annually**

^a^when necessary

^b^recommended

All the patients will be followed up according to the protocol every 3 months in the initial 3 years after the completion of treatment, every 6 months for an additional year, and every year thereafter. Follow-up examinations include complete history, physical examination, digital rectal examination, PSA, complete blood count, serum chemistry, CT of the chest, CT scan or ultrasound of the abdomen, mpMRI of the prostate, bone scan examination, and 68Ga-PSMA PET/CT which will be performed earlier if recurrence is suspected. Every patient is recommended to evaluate PSA at the same laboratory. In addition, quality of life should be assessed regularly during follow-up.

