## Methods/design

### Trial organization/coordination

This study is designed as an open-label, prospective, single-center, randomized two-armed (carbon ion radiotherapy vs. simultaneous integrated boost radiotherapy) study, primarily evaluating the differences in the severity and incidence of acute toxicity in patients with localized prostate cancer treated with carbon ion radiotherapy and simultaneous integrated boost carbon ion radiotherapy and further optimizing carbon ion therapy for prostate cancer. The rationale for this SIB approach is to provide a greater overall tumor-killing effect to prolong the biochemical recurrence-free survival without additional toxicity as compared with standard treatment. The two study arms are defined by different treatment strategy with arm A (carbon ion radiotherapy at 65.6 Gy in 16 fractions) and arm B (SIB carbon ion radiotherapy to the imaging-visible malignancy at 72Gy in 16 fractions). The flow chart of this phase II trial is illustrated in Fig. 1. The study carries out in Shanghai Proton and Heavy Ion Center (SPHIC) in China, and ethical consent was obtained from the ethics committee of SPHIC before trial initiation. The number of the ethics committee of SPHIC (Institutional Review Board) is 2006-62-03. All patients have written informed consent before inclusion in the trial.

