### Radiation therapy

#### Definition of target volumes and organs at risk

According to the risk factors of prostate cancer, there are three different definitions of clinical target volume (CTV). For the low-risk group, CTV is defined as the entire prostate; for the intermediate-risk group, CTV is defined as the entire prostate gland and inferior 1-1.5cm of seminal vesicles; and for high-risk and very high-risk groups, CTV is defined as the entire prostate gland and inferior 2–2.5cm of seminal vesicles.

The determination of the target boost area of prostate cancer is the key to the implementation of SIB technology. Based on the European Association of Urology (EAU) [30], the NCCN [2], and the European Society of Urogenital Radiology (ESUR) guidelines [31], mpMRI is used for the imaging diagnosis of prostate cancer due to its ability of great soft tissue resolution and the accuracy to distinguish between prostate tumors and normal prostate tissues [32]. A meta-analysis [33] of 29 prospective studies also showed that the sensitivity and specificity of mpMRI for the diagnosis of prostate cancer were 0.87 and 0.68, respectively. In addition, as a type II transmembrane protein, prostate-specific membrane antigen (PSMA) can be highly expressed in prostate cells, and its expression level is positively correlated with the stage and the grade of prostate cancer. 68Ga-PSMA PET/CT is assigned as an emerging diagnostic technique for prostate cancer based on PSMA molecular imaging. The positive diagnosis rate of prostate cancer can reach 69%, with 80% diagnostic sensitivity and 97% specificity, even 42% at very low PSA levels (<0.2 ng/ml) [34], and 68Ga-PSMA PET/CT has been gradually adopted clinically to guide radiotherapy planning for prostate cancer [35, 36]. Therefore, combined 68Ga-PSMA PET/CT and mpMRI might accurately locate the target area of prostate tumors, and CTV boost of the SIB group is defined as solid prostate tumors that are visible on mpMRI and 68Ga-PSMA PET/CT images in this trial.

The planning target volume (PTV) is defined as the CTV plus 8 mm in lateral (beam direction) and 5 mm anterior-posterior as well as in the inferior-superior margin.

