### Statistical analysis

The primary endpoint of the study is to observe the difference in acute toxicity in patients with localized prostate cancer who receive carbon ion radiotherapy and SIB carbon ion radiotherapy. All the patients will be randomly assigned to arm A and arm B in a ratio of 1:1. Assuming a type I error of 0.025 and type II error of 0.2, and under the assumption that the probability of no more than 2 degrees of acute GU and GI toxicities in arm A is 90% (Pc), and the probability of no more than 2 degrees of acute GU and GI toxicities in arm B is also 90% (Pt), with a non-inferiority margin of 0.15, we estimate that a sample size of 63 participants per arm will yield 80% power to show non-inferiority. However, anticipating a possible 10% dropout rate in each group, per arm *n* = 70 patients will be recruited into the study such that a total of *N* = 140 patients is required.

Statistical analysis will be performed using SPSS software (V20.0, SPSS Inc., Chicago, IL, USA). The Mann-Whitney *U* test will be used to compare the differences in acute and late toxicity between the two arms. The Kaplan-Meier method will be used to estimate the biochemical relapse-free survival, progression-free survival, and overall survival of the entire cohort. The association between each of the candidate prognostic factors with biochemical relapse-free survival, progression-free survival, and overall survival rates will be tested using the log-rank test. Multivariate analysis will be performed using the Cox regression model.

Analysis is planned on an intention-to-treat population (ITT), with all participants to be analyzed in the group to which they were randomized. We will make efforts to collect complete data for all participants and minimize missing data. If required, the missing data will be dealt with last observation carried forward method or multiple imputation.

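### The principal investigator both enrols and assigns patients, who are numbered only after assignment, so the stated procedure does not protect allocation concealment or leave a pre-assignment record

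*Protocol article*

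**What the plan says.** Patient assessments gives the roles: "Patients may be enrolled and randomized by the principal investigator in this trial once written consent has been obtained". It then describes the mechanism as 1:1 assignment "using computer-generated random numbers by the principal investigator, and sequentially numbered after being randomly assigned". Trial organization/coordination describes the design as "open-label, prospective, single-center, randomized two-armed".

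The primary endpoint is acute toxicity of grade 2 or higher (Duration of the study), graded by NCI-CTCAE version 4.03 (Evaluation of side effects). Statistical analysis sizes the trial for non-inferiority at 63 per arm, raised to 70 for dropout, and plans an intention-to-treat analysis. Data monitoring/auditing provides for regular audit by outside experts.

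The article describes no central service, envelopes, separate list holder or other separation between enrolment and assignment.

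**The concern.** Treatment cannot readily be masked in this trial, and the endpoint involves clinical judgement. Concealing the next assignment until a patient is irrevocably entered is therefore the main remaining protection against selection. It needs two things: the person who enters patients should not control the assignment, and a patient's entry should be recorded before the arm is known. The article fixes both the other way round. One role enrols and assigns, and the sequential number follows assignment.

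There is room for judgement at entry. The exclusion criteria end with open-ended items, such as any other condition that could interfere with particle therapy. Trial organization/coordination also states the investigators' expectation that the boost adds no toxicity. If patients thought prone to toxicity were entered less readily when the boost arm was due, arm B would look safer than it is. In a non-inferiority comparison of toxicity, that error favours declaring success.

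**Working it through.** **1. Order of steps, as stated.** Written consent, then randomisation by the principal investigator, then the sequential number.

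- *Separation of roles.* Enrolment and assignment are given to the same role, so the text contains no separation that would protect concealment.
- *Audit record.* A number issued after assignment cannot show that a patient was entered before the arm was known. A patient assigned and then dropped before numbering leaves no gap in the sequence. A patient whose assignment was drawn twice receives one number like any other.
- *What survives.* Consent comes first, so a dropped patient leaves a signed consent form with no trial number. An auditor could find that form. The form would not show whether the patient was dropped before or after the arm was known.

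**2. The plan's own figure.** Inputs from Statistical analysis: rates of 90% in both arms, margin 0.15, type I error 0.025 (read as one-sided), type II error 0.2.

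n = 2 × 0.90 × 0.10 × (1.960 + 0.842)² / 0.15² = 62.8, so 63 per arm. With 10% dropout, 63 / 0.90 = 70. Both stated figures are reproduced. Neither depends on who holds the sequence, so the fix leaves them unchanged.

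**3. Illustration of what selection could do.** The documents give no figure for selective enrolment, so the shift s below is an assumption. Take true rates exactly at the margin (90% in arm A, 75% in arm B) and 63 per arm. Suppose selection raises the observed arm B rate to 0.75 + s. Then

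SE = √[0.90 × 0.10/63 + (0.75 + s)(0.25 − s)/63], and type I error = Φ(s/SE − 1.960).

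| s (assumed) | SE | s/SE − 1.960 | One-sided type I error |
|---|---|---|---|
| 0 | – | −1.960 | 2.5% |
| 3 points | 0.0644 | −1.494 | 6.8% |
| 5 points | 0.0630 | −1.166 | 12.2% |
| 8 points | 0.0606 | −0.639 | 26.1% |

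The table shows the direction of the bias and how sensitive the error rate is to it. It does not estimate what has happened or will happen.

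**The case against.** The strongest reply is that this is a condensed article, that consent precedes randomisation, and that outside experts audit the trial. The first part does not remove the point, because the roles and the order of steps are stated, not left out. The other two parts limit how far it can be taken. Several stronger readings are tempting but unsupported.

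- *Allocation is not concealed.* The article never says the principal investigator can see the next assignment, and numbering after assignment does not reveal it. The text supports only that concealment is not protected. Nor does it say who takes consent for the trial; that sentence is passive.
- *The arms are not balanced on risk group.* Risk group sets the target volume, and endocrine therapy is "either neoadjuvant endocrine therapy or concurrent endocrine therapy, depending on their grading", so a reader might expect stratification. The article gives only a 1:1 ratio. It does not say that allocation is simple, and stratification or blocking may be set out in the full protocol. Silence here is no finding, and it gives no ground for asking for stratified blocks or covariate adjustment.
- *Selection would be undetectable.* The independent audit and the earlier consent forms contradict this. They make detection harder than it should be, not impossible.
- *Intention-to-treat would lose unnumbered patients.* The plan defines that population by randomisation, not by trial number. An assigned but unnumbered patient belongs in it; the risk is undocumented exclusion.
- *Steering two or three patients decides the trial.* At 10% event rates and 63 per arm the 95% half-width is 1.96 × √(2 × 0.10 × 0.90/63) = 10.5 points. That leaves 15 − 10.5 = 4.5 points, or 0.045 × 63 = 2.8 events. These are excess events, not steered patients. If high-risk patients had 20% to 30% toxicity (an assumption; the article gives no rate by risk group), removing 2.8 expected events would take about 2.8/0.30 = 9 to 2.8/0.20 = 14 exclusions, and more if they were replaced.

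**Conclusion.** The concern holds as a weakness in a stated procedure. In an open-label, single-centre trial with a clinician-graded primary endpoint, giving enrolment and assignment to one role and numbering patients afterwards leaves concealment unprotected. It also provides no pre-assignment record for audit.

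Its size cannot be derived from the documents. The type I error figures rest on an assumed shift, on true rates at the margin, and on the normal-approximation comparison that underlies the sample size. The conclusion about procedure rests on none of these. It does assume that the full protocol follows the roles and order given in the article. Nothing here implies misconduct or that the patients already allocated were selected. The change should be made, because it is cheap and removes an avoidable doubt about the primary comparison.

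**What to change.** For the remaining patients:

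1. Confirm eligibility, register the patient and issue the sequential number before allocation.
2. Have the sequence held and released, after registration, by an existing staff member who neither enrols patients nor grades toxicity. The principal investigator should have no access to it. Data collection and management mentions dedicated follow-up and data-entry staff. The article does not say whether they grade toxicity, so the sponsor should check this before choosing one of them.
3. Analyse every patient allocated, in the allocated arm.
4. Report all patients consented but not randomised. For those already entered, the signed consent forms can be reconciled with the trial numbers.

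The cost is a protocol amendment, which Protocol amendments says must go to the Institutional Review Board, and a short delay at each allocation. The sample size stays at 63 per arm, or 70 with dropout.

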### Radiation therapy

#### Definition of target volumes and organs at risk

According to the risk factors of prostate cancer, there are three different definitions of clinical target volume (CTV). For the low-risk group, CTV is defined as the entire prostate; for the intermediate-risk group, CTV is defined as the entire prostate gland and inferior 1-1.5cm of seminal vesicles; and for high-risk and very high-risk groups, CTV is defined as the entire prostate gland and inferior 2–2.5cm of seminal vesicles.

The determination of the target boost area of prostate cancer is the key to the implementation of SIB technology. Based on the European Association of Urology (EAU) [30], the NCCN [2], and the European Society of Urogenital Radiology (ESUR) guidelines [31], mpMRI is used for the imaging diagnosis of prostate cancer due to its ability of great soft tissue resolution and the accuracy to distinguish between prostate tumors and normal prostate tissues [32]. A meta-analysis [33] of 29 prospective studies also showed that the sensitivity and specificity of mpMRI for the diagnosis of prostate cancer were 0.87 and 0.68, respectively. In addition, as a type II transmembrane protein, prostate-specific membrane antigen (PSMA) can be highly expressed in prostate cells, and its expression level is positively correlated with the stage and the grade of prostate cancer. 68Ga-PSMA PET/CT is assigned as an emerging diagnostic technique for prostate cancer based on PSMA molecular imaging. The positive diagnosis rate of prostate cancer can reach 69%, with 80% diagnostic sensitivity and 97% specificity, even 42% at very low PSA levels (<0.2 ng/ml) [34], and 68Ga-PSMA PET/CT has been gradually adopted clinically to guide radiotherapy planning for prostate cancer [35, 36]. Therefore, combined 68Ga-PSMA PET/CT and mpMRI might accurately locate the target area of prostate tumors, and CTV boost of the SIB group is defined as solid prostate tumors that are visible on mpMRI and 68Ga-PSMA PET/CT images in this trial.

The planning target volume (PTV) is defined as the CTV plus 8 mm in lateral (beam direction) and 5 mm anterior-posterior as well as in the inferior-superior margin.

